### Health economics

Mean (and standard deviation) per patient costs and QALYs for the control and for the intervention(s) selected for the full 12-month evaluation through the adaptive trial design will be computed. Modelling will be used to extrapolate clinical events, costs and QALYs beyond the 12-month trial follow-up. Incremental analyses will be performed, with differences in costs and QALYs between alternatives calculated, and an incremental cost(s) per QALY gained will be estimated. Uncertainty around the cost per QALY value(s) will be quantified using non-parametric bootstrapping. Results from the economic evaluation will identify the intervention with the greatest probability of being cost-effective given the NHS’s willingness to pay for additional health gain.

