### Objectives

This paper describes the trial protocol for a large, pragmatic RCT to assess the effects of a physiotherapy intervention based on exercise or manual therapy compared to usual care for people with osteoporosis and a clinically diagnosed vertebral fracture.

The secondary objectives are: 1) to compare the effects of manual therapy with exercise therapy; 2) to investigate the acceptability and adherence to the physiotherapy programmes for both patients and therapists; 3) to conduct a parallel health economic analysis to assess the cost effectiveness of the different treatment strategies from an NHS, Social Services and patients’ perspective; and 4) to conduct a nested qualitative study to explore the experiences and views of people with osteoporosis and vertebral fracture regarding their treatment, their perceptions regarding the appropriateness and acceptability of the interventions and to explore the factors influencing their adherence to the intervention programmes.

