## Methods/Design

### Trial design

The trial will be a prospective, multi-centre assessor-blinded, three-arm RCT with a nested qualitative study and an adaptive design. Patients will be randomised between three arms: usual care (control) group (A), manual therapy (B) and exercise therapy (C). Those in the usual care arm will receive a single session of education and advice, and those in the active treatment arms (B + C) will be offered up to seven individual physiotherapy sessions over 12 weeks. Clinical assessment will be performed at baseline (week 0), 4 months and 12 months, with postal questionnaires about QoL administered at 6 and 9 months. An interim analysis will be conducted once 75 participants are recruited to each arm and have completed their 4 month follow-up. Following this interim analysis the study may be adapted. If both intervention arms are sufficiently promising and sufficiently similar the study will not be adapted and recruitment will continue into both intervention arms. If one arm, manual therapy or exercise therapy, is not sufficiently promising relative to control or sufficiently similar to the other intervention arm, this arm will be dropped from the study and the study will be adapted to continue as a two arm RCT with participants randomised between the control and remaining intervention arm. If neither arm is sufficiently superior to the usual care arm the trial will be stopped.

The protocol conforms to CONSORT guidelines for non-pharmacological studies [29] (Figure 1).

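### The only worded economic conclusion is the intervention most likely to be cost-effective, which need not be the strategy with the highest expected net benefit

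*Protocol article*

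**What the plan says.** The protocol article has two sections headed Health economics. The second, which follows Statistical analysis, sets out the economic analysis. Mean costs and QALYs are planned "for the control and for the intervention(s) selected for the full 12-month evaluation through the adaptive trial design will be computed". Incremental analyses follow, "with differences in costs and QALYs between alternatives calculated, and an incremental cost(s) per QALY gained will be estimated". On uncertainty it says: "Uncertainty around the cost per QALY value(s) will be quantified using non-parametric bootstrapping". It also plans a projection past the trial period: "Modelling will be used to extrapolate clinical events, costs and QALYs beyond the 12-month trial follow-up". It closes by saying that the results "will identify the intervention with the greatest probability of being cost-effective", judged at what the NHS is willing to pay.

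The Objectives make this a stated secondary aim of the trial: "to assess the cost effectiveness of the different treatment strategies". The number of strategies compared depends on the interim analysis. Under Trial design, all three arms continue on this condition: "If both intervention arms are sufficiently promising and sufficiently similar the study will not be adapted". Otherwise one active arm is dropped, or the trial stops.

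**The concern.** The closing sentence is the only place where the article says what the economic evaluation will conclude, and it attaches the conclusion to a probability of ranking first. A choice between strategies for a health service normally rests on expected net benefit: the mean health gain valued at the threshold, less the mean cost. The two criteria can part in two ways.

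- **Splitting.** With three strategies, two similar active arms share the replicates in which physiotherapy is best. Usual care can then lead on probability although both active arms have the higher mean. The trial keeps three arms only when the active arms look similar on QUALEFFO at the interim analysis, so this setting is a plausible one.
- **Skewness.** If the modelled gain beyond 12 months has a long upper tail, an option can have a positive expected gain and still be better in fewer than half of the replicates.

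At stake is which strategy the report names as preferred when the two criteria disagree, and whether the choice of criterion was fixed before the results were known.

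**Working it through.** The article states no cost, QALY, net benefit or threshold value, so there is no figure to reproduce. Every amount below is an assumption, chosen to show where the criteria agree and where they do not.

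**Set-up.** For strategy k, net monetary benefit is NMB = λ × QALYs − cost, where λ is the threshold. Criterion 1 picks the largest mean NMB. Criterion 2 picks the largest p, the share of replicates in which that strategy has the highest NMB.

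**Two strategies, normal errors.** p = Φ(Δ/SE of Δ), which exceeds 0.5 exactly when Δ > 0, so the criteria always agree. Example: Δ = £30, an SE of £50 in each arm and a further £150 of model uncertainty in the active arm. SE of Δ = √(50² + 50² + 150²) = 165.8, and Φ(30/165.8) = 0.57.

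**Two strategies, skewed gain.** Let the increment be exp(Z) − 1.2 with Z standard normal. Its mean is exp(0.5) − 1.2 = +0.45, but P(increment > 0) = 1 − Φ(ln 1.2) = 0.43. The criteria disagree.

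**Three strategies, equal means and equal SEs.** Let the active arms' errors have correlation ρ, with usual care independent of both. The two differences from usual care then have correlation (1 + ρ)/2, so p for usual care = 1/4 + arcsin((1 + ρ)/2)/(2π).
- ρ = 0: 1/4 + 0.5236/6.2832 = 0.333, an even split.
- ρ = 0.8: 1/4 + 1.1198/6.2832 = 0.428, leaving 0.286 for each active arm.

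So at ρ = 0.8 the active arms need a real advantage merely to draw level on probability.

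**Three strategies, simulated** (at least 1,000,000 draws per row, normal errors; ρ is between the active arms unless stated; advantage is over usual care).

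| SEs (£): usual care / active / active | ρ | Advantage (£) | p (%): usual care / active / active | Criteria |
|---|---|---|---|---|
| 300/300/300 | 0 | 44, 44 | 29/35/35 | agree |
| 300/300/300 | 0.8 across all three arms | 44, 44 | 25/38/38 | agree |
| 300/300/300 | 0.4 | 44, 44 | 33/33/33 | tie |
| 100/100/100 | 0 | 30, 25 | 26/38/36 | agree |
| 200/400/400 | 0 | 44, 44 | 24/38/38 | agree |
| 200/400/400 | 0.8 | 44, 44 | 37/31/31 | disagree |
| 200/200/200 | 0.5 | 20, 20 | 36/32/32 | disagree |
| 200/80/80 | 0 | 30, 20 | 37/34/29 | disagree |
| 150/400/400 | 0 | −50, −50 | 32/34/34 | disagree |
| 150/120/180 | 0 | 100, 80 | 18/42/39 | agree |
| 150/120/180 | 0 | 100, 90 | 18/41/41, second active arm just ahead | disagree |

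Unequal SEs do not always cause disagreement. The independent 200/400/400 row agrees and the 200/80/80 row does not.

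**How close the means must be.** At ρ = 0.8, usual care leads on probability up to an active advantage of about £104 with SEs of £300 in every arm, and up to about £87 with 200/400/400. Against the SE of an active-minus-usual-care difference, these are 104/√(300² + 300²) = 104/424 = 0.25 and 87/√(200² + 400²) = 87/447 = 0.19. In these settings the reversal is confined to differences of at most a quarter of a standard error.

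**The case against.** The strongest reply is that the sentence describes an output and is not worded as an adoption rule. The same section plans mean costs, mean QALYs and incremental ratios, from which the strategy with the highest expected net benefit follows at any threshold. This stands. A reader might infer that the trial will choose its recommendation by probability alone, but the text does not say so.

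A second reply is that three strategies reach the analysis only if neither active arm is dropped. The Sample size section puts the chance of dropping an arm no better than control at about 73%. With two strategies, disagreement needs skewness, on which the article gives no figures. This also stands and limits the scope.

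A third is that disagreement depends on chosen inputs: several reasonable sets agree, the disagreements are near-ties, and nothing in the article confines extrapolation uncertainty to the active arms. That is correct, and the agreeing cases are shown for that reason.

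A fourth is that an article leaves such detail to a health economics plan. This carries less weight, because the criterion is stated here, not left out. A fuller plan may already rest the conclusion on expected net benefit.

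A reader might also infer that a percentile interval for the cost-per-QALY ratio is planned, which would be hard to interpret if QALY differences straddle zero. The article names bootstrapping but no such interval. The probability it refers to can be found by comparing each replicate's cost and QALY pair with the threshold, which works on both sides of zero.

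**Conclusion.** The point holds as a minor one. The right quantities are planned, but the only conclusion in words is tied to the probability of ranking first, which is not the same criterion as expected net benefit. The two can differ if both active arms continue and uncertainty is correlated between them or unequal across arms, or if modelled gains are skewed. In the three-strategy examples the means must also be close relative to their standard errors. With equal, independent errors, or two strategies with symmetric errors, they agree. At an equal SE of £300 and a £44 advantage, the switch comes at an active-arm correlation of about 0.4.

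How likely or how large a reversal would be in this trial cannot be judged, because the documents contain no economic figures. They do not support saying that the plan will lead to a wrong recommendation, only that the criterion as worded would permit one.

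**What to change.** Reword the closing sentence of the second Health economics section. The preferred strategy, among usual care and the intervention(s) continuing after the interim analysis, is the one with the highest expected net monetary benefit at the stated NHS threshold. Comparing incremental costs per QALY with that threshold after a full incremental analysis is equivalent. Report the bootstrap probability of being cost-effective for each strategy as a description of uncertainty around that choice. If a separate health economics plan already says this, align the article's sentence with it.

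The cost is one or two sentences. The same bootstrap replicates serve and no further data are needed. Settling it before results are seen also prevents a later choice between criteria if they disagree.

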### Timeline

The trial is funded to run over a period of 51 months and commenced in January 2013. The final follow-up visit for the final participant is projected to be completed by the end of month 42 (that is, by June 2016). Data analysis, economic analysis and report writing will be from month 45 onwards.

## Discussion

Osteoporosis and vertebral fracture have a considerable impact on an individual’s health-related QoL due to pain, limitations in activity and social participation and altered mood. The need to develop effective treatment approaches for osteoporosis and to decrease the health burden of associated vertebral fractures is an important clinical and research objective. This pragmatic RCT will provide high quality evidence of the longer term clinical and cost effectiveness of two physiotherapy-based interventions. Overall, there is evidence of proof of concept that both manual therapy and exercise interventions can be beneficial for this patient group. However, currently there are questions about compliance with exercise programmes and whether a positive effect can be seen at levels of intervention intensity that are deliverable within current NHS resources. This trial design allocates equivalent physiotherapist contact time to participants in each intervention group and broadly reflects current outpatient physiotherapy resources within the NHS which should assist with delivery and generalisability of any findings.

Our study offers a novel approach in using an adaptive trial design to assess the efficacy of a rehabilitation intervention. At the outset the plan is to conduct a multi-centred, three-arm RCT with blinded assessments. The justification for using an adaptive design is that this is a new and emerging area of clinical practice. Instead of offering a “black box” of combined manual and exercise therapies, we have a chance to estimate the effects of these treatment strategies in isolation. Each is indicated for adults with symptomatic osteoporotic vertebral fracture. There are some reported concerns with the efficacy and safety of spinal mobilisation [10,11], thus there is merit in testing manual therapy in isolation against an exercise-based intervention. Additionally, spinal mobilisations are the most expensive physiotherapy modalities to deliver as they cannot be self-administered, and require individual sessions. Using an adaptive design allows the trial to be adapted to a two-arm trial, with resulting increased power, should one of the intervention arms be assessed as ineffective at interim analysis. If neither intervention shows benefit, the trial would be stopped early using futility rules. We believe that this adaptive design has merits over testing a multi-modal programme of combined exercise and manual treatments where it is difficult to evaluate the efficacy of individual components. There would also be significant concerns about the safety and cost of some aspects of the multi-modal programme, that make isolating the interventions an attractive option in terms of new knowledge gained.

Importantly, the pragmatic approach offered in this trial allows programmes in both intervention arms to be individualised with regard to the content and intensity level of the exercise or manual therapy technique. This makes it less artificial than many RCT intervention designs and thus much closer to normal clinical practice.

Our study is the first large-scale RCT to investigate the effect of different physiotherapy management strategies – exercise or manual therapy intervention for patients with osteoporosis and vertebral fracture. We plan to recruit 600 patients to the trial. Even if the adaptive design and interim analysis rules proved that neither intervention were effective and the trial was stopped on the grounds of futility, it will still be the largest RCT conducted of physiotherapy and osteoporosis. Strengths of the study design are the pragmatic nature of treatment delivery by practicing physiotherapists in NHS physiotherapy clinics across the UK, as well as the reproducibility of both the physiotherapy intervention programmes. These features will improve the ability to translate the findings into a standard practice and enable future delivery of the intervention to be given within existing NHS resource levels and the constraints of a publically funded health system.

In addition to this paper, updated versions of the protocol if amended throughout the trial will be available on the trial website (http://www.ndorms.ox.ac.uk/clinicaltrials/prove) and will follow SPIRIT 2013 guidelines [45].

## Trial status

The first patient was randomised to the trial in September 2013. Recruitment for the study is ongoing.

## Abbreviations

BMD: bone mineral density; IDMC: independent data monitoring committee; NHS: National Health Service; PROVE: Physiotherapy Rehabilitation for Osteoporotic Vertebral Fracture; QALY: quality-adjusted life year; QoL: quality of life; RCT: randomised controlled trial; TLS: Timed Loaded Standing.
